### Software

Data will be processed and analyzed using the most current and reliable version of Praat [26], Audacity [27], Python [28], R (R Core Team) [29,30], and OpenSmile [24].

**Figure 4 figure4:**
[figure not shown]
Quantile-quantile plot of residuals from model 1A with end point *v_j_*. Data are simulated and placeholders for results.

**Table 1 table1:** Summary of fixed effects for *v_j_*. Data are simulated and placeholder for results.

Effect	Estimate	SE	*t* test	*df*	*P* [r(>|*t*|)] value
Intercept (*μ*)	1.16	0.12	9.54	4.99	2.15×10^–^^4^
Age (*α*)	0.49	0.01	51.23	4.99	5.36×10^–^^8^
Gender (*γ*)	0.83	0.13	6.16	4.99	1.64×10^–^^3^
Diagnosis (*δ*)	0.94	0.04	22.95	4.99	2.92×10^–^^6^
Age:gender (*ν*)	0.02	0.01	1.19	4.99	2.87×10^–^^1^

**Table 2 table2:** Summary of simulated random effects *v_j_* with 100 observations and 10 groups (youth).

Groups	Variance	SD
Youth (*σ_y_*)	2.29×10^–^^3^	4.79×10^–^^2^
Residual (*σ_e_*)	2.33×10^–^^3^	4.83×10^–^^2^

**Table 3 table3:** Simulated CIs for effects on *v_j_*.

Effect	Effects (%), CI	
	2.5%	97.5%
*σ_y_*	1.87×10^–^^2^	5.73×10^–^^2^
*σ_e_*	4.2×10^–^^2^	5.63×10^–^^2^
Intercept	9.71×10^–^^1^	1.34
Age	4.76×10^–^^1^	5.05×10^–^^1^
Gender	6.23×10^–^^1^	1.04
Diagnosis	8.74×10^–^^1^	9.99×10^–^^1^
Age:gender	–4.16×10^–^^3^	3.34×10^–^^2^

### Statistical Report Model 1B

We shall first assess the assumptions of our model by examining the surrogate residuals in a quantile-quantile (q-q) plot (see Figure 5). In this case, the assumptions are violated as the residuals are not normally distributed. In case the assumptions are violated, we will not report on parameter estimates and their confidence intervals, as these will not be meaningful. However, we can still use the model for predictions.

Figure 6 illustrates the receiver operating characteristic (ROC) curve for the training data, and the estimated classification accuracy is 80%. Additionally, we will report sensitivity, specificity, area under the curve, and a confusion matrix, similar to the next section.

If the surrogate residuals show an approximated normal distribution in the q-q plot, we will report parameter estimates, etc, as we have for model 1A.

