## Methods

### Participants and Setting

We will include audio recordings from a total of 64 youths aged 8 to 17 years (47 with OCD and 17 healthy controls). The audio recordings of diagnostic interviews stem from a large randomized clinical trial and case-control study of OCD, called TECTO [17]—TECTO runs at a public hospital in Denmark.

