### Statistical Analysis Plan

The planned study has two main objectives:

Test the usefulness of a previously learned latent model, composed of 2 dimensions representing a compressed vocal feature space guided by activation labels [16], as a marker for OCD diagnosis and severity.Learn a new latent model, which we will propose as an improved candidate indicator of OCD severity.

Our first objective will be achieved through 2 statistical analyses, with the following hypotheses:

Objective 1 (H1): an ANOVA will be conducted to test the first research hypothesis (objective H1A) that there is an effect of diagnosis (OCD vs no psychiatric diagnosis) on the vocal feature latent model. With logistic regression (H1B), we will test hypothesis H1, which states that there is an effect of the vocal feature latent model on OCD severity classifications in moderate to extreme OCD cases, with the vocal feature latent model corrected for age and gender. This analysis will only include patients with OCD, and we will examine the classification accuracy of this model.Objective 2 (H2): the second objective will be achieved through data labeling and machine learning modeling. Here, outcomes will include diagnostic status (OCD vs no psychiatric diagnosis) and OCD severity (CY-BOCS severity scores). We will validate the modeling using a leave-two-individuals-out cross-validation and prediction accuracies. Subsequently, we will assess the obtained results using an independent test. We will extract data from 10 of the youths’ audio samples post machine learning modeling for this purpose.

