#### Statistical Models for Objective H1B

We will use a logistic regression with OCD severity categories moderate and severe-extreme as the outcomes. We denote the severity *s* = 0, 1. We will fit the following logistic regression model to the scores:

logit(si) = θ + b1

i + b2

i + εi (2)

where *ε_i_* ∼ *N* (0, *σ*_2_*_j_*) and v*_j_* is the *j*th latent vocal feature adjusted for age and gender and averaged over the 10 repetitions for each youth, as described in the following.

This analysis aims to test the effects from vocal features on the severity scores through the null hypotheses that *b*_1_ = 0 and *b*_2_ = 0, which we will test at a 1.25% level of significance.

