#### Adjusting for Multiple Testing

We are interested in the null hypotheses associated with the effect of a diagnosis on the two dimensions in the latent model as well as the effects from the two adjusted latent dimensions on the severity scores. We will adjust our 4 *P* values using the Bonferroni method, and thus test each null hypothesis at a 5%/4=1.25% level of significance resulting in a family-wise error rate for the four tests of 5%.

#### Machine Learning Models for Objective 2

To improve the vocal features for possible use as biomarkers of OCD severity, we shall use the following methodology. First, 2 authors ([name]) will annotate samples for activation and valence on a 5-point Likert scale with 1 indicating low activation and 5 indicating high activation. We shall only provide the annotators with one speech segment at a time in a blinded manner and in random order.

For the planned analyses, we will not use the valence labels, but the activation labels as these labels have shown promise in previous investigations [16]. We will use these labels as in our previous work [16]. The major advantages of labeling speech signals with activation scores include making labels for Danish speech and for children’s speech, and labeling speech of patients and controls. Thus, the labels provide added information as no open source data exist, thus supporting transfer learning wherever feasible.

Subsequently, we shall train the following machine learning models using the following annotations: variational and denoising autoencoders with semisupervised losses based on activation labels and a reconstruction error, plus a logistic regression or logistic regression loss in a neural network to obtain a classification model.

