**Figure 6 figure6:**
[figure not shown]
Receiver operating characteristic curve for the training data.

### Statistical Report Model 2

The evaluation results of the machine learning model on simulated results are reported using the classification metrics in Table 4, the ROC curve in Figure 7 and the confusion matrix in Figure 8. The results will be presented for the validation data (the left-out youth) over the cross-validation to select hyperparameters and a model. We will also compare to the same measures for the training data to assess the amount of possible overfitting. Final results will be provided for the independent test data consisting of 10 youths.

**Table 4 table4:** Simulated classification performance.

Evaluation metric	Value (normalized)
Accuracy	0.82
Sensitivity	0.78
Specificity	0.86
Area under the curve	0.89

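### Model 1B's ROC curve, and by the natural reading its accuracy and related metrics, come from the patients used to fit it, and no validation in the plan fits this patients-only model

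*Protocol article*

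**What the plan says.** All references are to the Protocol article.

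- **Participants and Setting** gives the sample as "47 with OCD and 17 healthy controls".
- **Statistical Analysis Plan**, on H1B: "This analysis will only include patients with OCD, and we will examine the classification accuracy of this model".
- **Statistical Models for Objective H1B**: "We will use a logistic regression with OCD severity categories moderate and severe-extreme as the outcomes". The predictors are the two latent vocal features, adjusted for age and gender and averaged over ten segments per youth. The tests concern the "null hypotheses that *b*_1_ = 0 and *b*_2_ = 0, which we will test at a 1.25% level of significance".
- **Statistical Report Model 1B**: Figure 6 "illustrates the receiver operating characteristic (ROC) curve for the training data, and the estimated classification accuracy is 80" per cent. The next sentence promises sensitivity, specificity, AUC and a confusion matrix, in the manner of the section that follows. If the surrogate residuals look non-normal, parameter estimates and confidence intervals are not reported, but the model may still be used for prediction.
- **Figure 6 caption**: "Receiver operating characteristic curve for the training data".
- **Model Validation Strategies**: the cross-validation leaves out one control and one patient per fold and tunes the machine learning models. A test set of 5 patients and 5 controls evaluates those methods.
- **Statistical Report Model 2**: left-out results are compared with training results to gauge overfitting, for Model 2 only.

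**The concern.** Performance measured on the data that produced the coefficients is biased upward, because the fit has already used the chance associations in those data. The plan guards against this for Model 2 and states no equivalent guard for H1B, although classification accuracy is a declared H1B output.

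The fallback rule adds weight. If the residual check fails, as it does in the plan's simulated illustration, the effect estimates and intervals are withheld and the classification metrics become the main reported H1B result. A reader would then judge whether voice tracks severity largely from figures with no correction for optimism. Accuracy is also hard to interpret without the rate obtained by always predicting the larger class, and the plan does not say it will set the two side by side.

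**Working it through.** **The plan's own figures.** The 80% accuracy comes from placeholder simulated data whose generating values and class split are not given, so it cannot be reproduced. The one nearby figure that can be checked, 5%/4 = 1.25%, is right.

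**Does any stated validation cover H1B?** H1B contains patients only. A fold made of one control plus one patient cannot be formed from that set. The cross-validation and the independent test are both placed under Objective 2 and tied to newly learned models. No H1B hold-out is defined.

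**Inputs for sizing the optimism.**
- n = 47 patients (Participants and Setting). If the 5 test patients are drawn from these, n = 47 − 5 = 42.
- Two predictors plus an intercept (Statistical Models for Objective H1B).
- Split between moderate and severe-extreme: not stated, so varied as an assumption.

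**Method.** Simulate two independent standard normal predictors unrelated to severity, fit the logistic regression by maximum likelihood, and score it (a) on the fitting data and (b) on 2,000 new subjects. Accuracy uses a cut-off of 0.5. There were 3,000 runs per split. Optimism = mean training value − mean new-data value.

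| n (severe) | Majority rate | Training AUC, mean (5th–95th percentile) | New-data AUC | Training accuracy | New-data accuracy | Accuracy optimism |
|---|---|---|---|---|---|---|
| 47 (23) | 51.1% | 0.605 (0.52–0.71) | 0.500 | 57.6% | 50.1% | 7.5 points |
| 47 (19) | 59.6% | 0.607 (0.52–0.71) | 0.500 | 61.6% | 56.8% | 4.8 points |
| 47 (14) | 70.2% | 0.615 (0.52–0.73) | 0.501 | 70.7% | 68.6% | 2.1 points |
| 42 (21) | 50.0% | 0.611 (0.52–0.72) | 0.500 | 58.0% | 50.0% | 8.0 points |
| 42 (13) | 69.0% | 0.616 (0.52–0.73) | 0.500 | 69.7% | 67.1% | 2.6 points |

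AUC optimism is 0.605 − 0.500 = 0.105 at the balanced split and 0.615 − 0.501 = 0.114 at 14 of 47. In the three n = 47 rows, training AUC reaches 0.60 in 50 to 56% of null runs and 0.70 in 6 to 10%.

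**Why accuracy needs the majority rate.** At an extreme split of 9 to 38, always predicting the larger class gives 38/47 = 80.9%, and training accuracy reaches 80% in about 93% of null runs. In the table's n = 47 rows it does so in fewer than 0.5%. The same 80% could therefore mean nothing or a good deal, depending on the split.

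**Which correction works.** Under the same null (true AUC 0.50), n = 47:
- Stratified 5-fold cross-validation with AUC computed within folds: mean AUC 0.496 (23 severe) and 0.499 (14 severe); mean accuracy 49.8% and 68.1%.
- Bootstrap optimism correction: mean AUC about 0.53 to 0.54, so a little optimism remains.
- Leave-one-patient-out with pooled predictions: mean AUC about 0.39, clearly too low. Leaving out a patient shifts the fitted intercept against that patient's own class, which distorts the pooled ranking.

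**The case against.** Several points on the other side stand.

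- **The bias is modest.** The latent features come from a network pretrained on external speech, and H1B estimates only an intercept and two slopes, with no tuning. A reader might infer that noise would look strongly predictive. The figures do not support that: it typically gives an AUC near 0.6, and an accuracy of 80% is rare unless the classes are very unequal.
- **The confirmatory result is untouched.** The plan will "test each null hypothesis at a 5%/4=1.25% level of significance", and the tests of the two slopes do not depend on training accuracy.
- **The labelling is partial.** Only the ROC curve is expressly said to be on training data. The accuracy shares its sentence, while the other metrics name no data set and point to the next section, which does report left-out and test results. One could read that as borrowing Model 2's validation. The more natural reading is that it borrows the list of metrics, since the Model 2 folds cannot be applied to patients alone. It remains a reading.
- **Class counts will be visible.** A confusion matrix lets a reader work out the majority rate, and sensitivity and specificity would expose a classifier that always picks one class. Stating the rate is a help to the reader and does not fill a gap in the data.
- **The 80% proves nothing.** A reader might take it as evidence of inflation. It is simulated and shows only the reporting template.
- **The fallback is conditional.** It operates only if the residual check fails. The text names estimates and intervals as withheld and does not expressly withdraw the tests, so it goes too far to say that training accuracy would be the only H1B result.

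None of this supplies a validation for H1B. An open training label tells the reader where the curve came from but does not give the corrected value.

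**Conclusion.** The point holds as a reporting weakness that should be fixed before the analysis. It does not invalidate the H1B hypothesis tests. Followed as written, the plan gives H1B a ROC curve, and by the natural reading an accuracy and related metrics, with optimism of about 0.11 in AUC and about 2 to 8 percentage points in accuracy when the vocal features carry no information.

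These sizes assume two independent normal predictors, 42 to 47 patients, a cut-off of 0.5 and 30 to 50% severe. The simulation did not include the prior age and gender regression. That all 47 patients enter H1B is inferred from the sample description and the patients-only statement; using 42 does not change the conclusion.

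**What to change.** For model 1B, state that AUC, accuracy, sensitivity and specificity will come from one of two patients-only procedures, chosen now:

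1. repeated stratified k-fold cross-validation, with AUC computed within folds and then averaged; or
2. bootstrap optimism correction.

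In either case, re-estimate the regression described under Adjusting for Confounding and Calculating Average Features inside every training fold or resample. Do not use pooled leave-one-out AUC, which is biased low. Print the majority-class accuracy beside the corrected accuracy. Keep the training ROC curve and metrics if wanted, labelled as apparent.

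The cost is a little extra computation on a very small model and less favourable figures. No new data are needed. Fixing the choice in advance also prevents the result from deciding which version is shown.

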**Figure 5 figure5:**
[figure not shown]
Quantile-quantile plot of surrogate residuals from model 1B with endpoint *v_j_*. Data are simulated and placeholders for results.

**Figure 6 figure6:**
[figure not shown]
Receiver operating characteristic curve for the training data.

### Statistical Report Model 2

The evaluation results of the machine learning model on simulated results are reported using the classification metrics in Table 4, the ROC curve in Figure 7 and the confusion matrix in Figure 8. The results will be presented for the validation data (the left-out youth) over the cross-validation to select hyperparameters and a model. We will also compare to the same measures for the training data to assess the amount of possible overfitting. Final results will be provided for the independent test data consisting of 10 youths.

**Table 4 table4:** Simulated classification performance.

Evaluation metric	Value (normalized)
Accuracy	0.82
Sensitivity	0.78
Specificity	0.86
Area under the curve	0.89

**Figure 7 figure7:**
[figure not shown]
Receiver operating characteristic curve for the classification model. AUC: area under the curve; OCD: obsessive-compulsive disorder.

**Figure 8 figure8:**
[figure not shown]
Confusion matrix for the classification model. OCD: obsessive-compulsive disorder.

## Discussion

### Expected Findings

In this paper, we describe the methods and analysis plan for testing the effects of OCD diagnosis and symptom severity on vocal features in the youth. We anticipate that we can improve the methods that model these putative associations. Through this work, we aim to obtain reliable transdiagnostic indicators of clinical severity from voice that would serve as valuable monitoring tools in psychiatry [31]. Additionally, the vocal indicators obtained from this work, in tandem with additional data modalities including video and semantics of the speech conversation, will be employed in multi-sensor modeling of OCD behavior in future work [32]. The results described in this analysis plan will be published in relevant scientific journals.

### Strengths

A major strength of the planned study is this documentation of the analysis plan prior to performing analyses. Documented a priori hypotheses prevent unscientific practices such as selectively reporting significant results [33]. Furthermore, diagnostic status and OCD severity levels were established by trained mental health professionals using gold-standard clinical interviews. Another strength of the planned study is that we will include gender in the models. Compared with male speech, female speech is marked by a higher pitch. A study found that gender-specific models were more accurate in detecting sadness and positive and negative affect than gender-independent models [34]. Depressed speech is marked by reduced pitch, whereas anxious speech is marked by increased pitch [10].

Another study found that pitch appears more important for detecting stress in men while Root Mean Square Energy appears more influential in detecting stress in women [35]. Thus, if training data sets are overrepresented by one gender, an automatic depression or anxiety severity rating algorithm may misclassify speech by other genders. We also attempted to strengthen our analyses by adding age to the models. The available latent model that we will use in our study of youth of a wide age range were trained on adult speech. With age, pitch and formant frequencies tend to decrease [36]. From childhood to adolescence, speech rate increases, and conveying emotions with prosodic cues, including pitch and timing, is a development feat [37].

### Limitations

The planned analyses have some foreseeable challenges. First, we plan to recruit a small sample. Preprocessing and data labeling, required for the planned analyses, are time-consuming tasks. Our small sample size increases the risk of type II errors. Machine learning techniques are more robust as we can improve models by adding more labeled data and testing on a new independent data set. Second, the audio samples that will be analyzed were collected for clinical purposes and not under optimal conditions for audio feature extraction and analysis (ie, using high quality microphones in a quiet environment). Thus, methods developed on these data will likely translate well to other naturalistic settings [38-41]. Finally, this study focuses on the associations among OCD diagnosis, severity, and vocal features in the child. In future work, we will study the effect of OCD diagnosis on vocal features while accounting for secondary diagnoses and investigate the influence of clinician’s vocal characteristics on the vocal features of the child.

### Conclusions

This predefined plan will limit bias in the interpretations and conclusions of the reported results of the future publication. If the results in the planned study are promising, this will be a step toward using vocal sensing to automate objective assessments and monitoring of severity of psychiatric disorders such as OCD.

## Abbreviations

CBT: cognitive behavioral therapy
CY-BOCS: Children’s Yale-Brown Obsessive Compulsive Scale
ERP: exposure and response prevention
K-SADS: Kiddie Schedule for Affective Disorders and Schizophrenia
OCD: obsessive-compulsive disorder
q-q: quantile-quantile
ROC: receiver operating characteristic
